## 5 TREATMENT

### 5.1 Investigational Medicinal Product (IMP)

For this study the IMP is:

**INOMax 800 ppm mol/mol delivered** by the INOBlender, is defined as the Investigational Medicinal Product (IMP). The study set up is depicted in 5.3.1.

The INOMax + INOBlender set up described is added onto the standard set up in the service for the administration of medical oxygen on bag-mask system. There are no alterations to either drug or drug delivery system in this trial outside of approvals given for the equipment and its use.

### 5.2 Drug Identity, Supply and Storage

The drug studied, inhaled nitric oxide, will be delivered by Linde Healthcare (Linde Gas AB – Linde Healthcare, [name], Sweden) as INOMax 800 ppm 2 Litre gas cylinders. They will be stored at Lørenskog Helicopter base in accordance with the specifications laid out in the SPC. The INOMax gas cylinders for this trial will be stored separate from the gas cylinders used in other clinical practice.

All documentation relating to the order, delivery and receiving of INOMax 800 ppm mol/mol for this trial will be kept in the TMF with a drug accountability system being in place for the identification of batch numbers of gas-cylinders and which INOBlender was used at each patient.

### 5.3 Dosage and Drug Administration

In this trial we follow the SPC of INOMax and start dosing at 20 ppm. We will not allow doses above this within this protocol. Weaning will follow standard practice. The duration of treatment is significantly lower than with the SPC, due to the objective of the trial- increased oxygen saturation prior to RSI

After 3 minutes on standard treatment (O2 12l/min + 10 cm H2O PEEP) patients with a SpO2 between 50 and 90% will be randomized. For patients randomized to O2 + Inhaled nitric oxide the drug will be administered in the following way:

- INOMax 800 ppm mol/mol will be administered by the INOBlender (IMP) at 20 ppm by bag-mask ventilation. O2 and PEEP is continued as per standard treatment. If inadequate spontaneous breathing, the doctor should use the bag to support ventilation in accordance with existing guideline. INOMax at the dose of 20 ppm will be delivered for 5 minutes before any attempt to intubate (or decision not to) will be made.

- After 5 minutes RSI may be performed at the discretion of the study doctor in accordance with departmental procedure for RSI in this category of patients.
- Following RSI, the ventilation bag is squeezed the 3-4 times with O2 / INO before starting ventilation. This is to empty the bag of any NO2 that may have been built up.
- Regardless whether RSI is performed, or bag/mask ventilation is continued, a dose reduction of iNO should be attempted if SpO2 ≥ 94% after 5 minutes (t1)
- Reduction is made in steps of 5 ppm every 5 minutes unless SpO2 drops by > 5 percentage points from the value at t1.
- In case weaning is completed during transportation, self-expandable bag ventilation may be substituted with a mechanical ventilator.
- After arrival in hospital, when patient is intubated, or a decision not to intubate has been made, iNO administered by INOBlender should be weaned by 5 ppm every 5 minutes. In the unlikely event of a rebound effect (as assessed by the study doctor) iNO may be continued temporarily as necessary. INO administered by other devices (i.e.: not IMP) may be initiated as per local routines at the discretion of the attending doctor taking over the responsibility for the patient.

The total duration and concentration of IMP the patient has received will be recorded in the CRF.

### 5.3.1 INO delivery system and study setup

[figure not shown]

1. INOmax ® Nitric Oxide 800 ppm mol/mol, Linde Healthcare AB (EU/1/01/194/001, EU/1/01/194/002)
2. Conoxia ®, Medical Oxygen 100%, Linde Healthcare AB (N 06-4045)
3. INOBlender ® Mallinckrodt Pharmaceuticals
4. Ambu Spur II ®, Oxygen Hose, AMBU A/S
5. Ambu Spur II ®, Oxygen Reservoir, AMBU A/S
6. Ambu Spur II ®, Adult Resuscitator self-expandable bag, AMBU A/S
7. Disposable PEEP 20 valve®, AMBU A/S
8. CapnoAdaptor Corpulse
9. HEPA filter
10. Face mask

The INOBlender (3) is a CE certified device for blending medical oxygen and INOmax. The blender is connected to one cylinder of CONOXIA (2) and one cylinder of INOmax (1). The INOBlender is connected to a self-inflating resuscitator bag (6), with a reservoir (5) through a dedicated tubing (4). Gas flow into the bag is diverted either to the main bag, or the reservoir. By spontaneous breathing or by squeezing the bag, gas flows from the bag and the reservoir through a flap valve in the direction of the patient. The gas flows through the in-line capnography adapter (8) and the HEPA-filter before entering the face mask (10). On Exhalation gas from the patient flows in the reverse direction and exits through the PEEP valve (7). During the study period the hospital may change suppliers of some of these components. These will be incorporated into the trial setup without applying for protocol amendments but recorded in the TMF. No changes to INOblender or INOmax is allowed without notifying competent authority. The total received dose will be calculated based on INO concentrations and duration.

## 5.4 Premedication and Monitoring

### 5.4.1 Premedication:

- Medical oxygen is mandatory in all patients included and will be recorded in the CRF
- All other medications administered by treating physician prior to IMP will be recorded in the CRF

### 5.4.2 Monitoring and equipment

Minimal monitoring prior to administering IMP, and recorded in the CRF is:

- Pulse oxygen saturation
- EtCO2
- Resuscitation pads
- Blood pressure monitoring: Non-invasive or arterial line
- Vascular access: central or peripheral intravenous lines or intraosseous access

Additional monitoring if available:

- Near-infrared spectroscopy (NIRS) cerebral oxymetry
- Pulse induced continuous cardiac output (PiCCO)
- Arterial blood sampling for blood gas analysis
- Central venous pressure

## 5.5 Concomitant Medication

### Non- IMP to all patients in this trial:

**Medical oxygen** (ATC: V03AN01) Medicinal gas, compressed. Current Trade Name: Conoxia 100 % . Oxygen will be delivered using standard and non-modified equipment, and connected to INOBlender as shown in 5.3.1. It will be delivered at a rate of 10 Litre/ minute. Please see attached SPC (in Norwegian)

- No medication excludes participants from being included in this trial.
- Medical oxygen will be delivered to all patients included in this trial.
- Medications used by patients prior to acute illness and inclusion in this trial will be recorded if information is available at the time of inclusion.
- All medications administered as part of emergency treatment and intubation will be recorded in the CRF. It is expected that patient will be treated with sedatives such and ketamine or propofol, opioids such as fentanyl and neuromuscular blockers such as rocuronium bromide. Medications will be recorded as ATC number, generic name, dose and route of administration. The list below is an example of the most common medications used, this is not exhaustive. A search at [interaksjoner.no](http://interaksjoner.no) between these listed medications with R07A X01 Nitrogenoksid does not yield any interactions. That search also informs us that the database is not updated. The SmPC does states some caution with concomitant use of prilocaine, a local anesthetic not used in emergency medicine. This is a very unlikely happening, and if co-administered will be noted in the CRF.

| Common medication in Air Ambulance setup (In Norwegian) |                                |
|---------------------------------------------------------|--------------------------------|
| Adenosin life inf/inj 5mg/ml                            | Lidokain mylan inj 20mg/ml     |
| Adrenalin base NAF injkons 1mg                          | Magnesiumsulfat inf kons 1mmol |
| Adrenalin takeda inj 0,1mg/ml                           | Metalyse inj subst 10000U      |
| Adrenalin takeda inj 1mg/ml                             | Midazolam braun inf/inj 1mg/ml |
| Aminophylline amd inj 25mg/ml                           | Na kl braun inf 9mg/ml Eco+    |
| Amiodaron ham inf/inj kon 50mg                          | Na kl braun infkon 1mmol/ml MP |
| Aspirin inf/inj subst 500mg                             | Na kl fres t par br 9mg/ml pl  |
| Atropin takeda inj 1mg/ml                               | Naloxon hamel inf/inj 0,4mg/ml |
| Atrovent inh væske 0,125mg/ml                           | Nifedipin AL kaps 10mg         |
| Bricanyl inj 0,5mg/ml                                   | Nitrolingual munnspr 0,4mg/dos |
| Calciumklorid inf kons 1mmol                            | Noradrenalin abc infkon 1mg/ml |
| Cefotaxim mip inf/inj subst 2g                          | Ondansetron hameln inj 2mg/ml  |
| Curacit inj 10mg/ml                                     | Oxytocin or inf/injkons 5 IE   |
| Deksklorfeniramin NAF inj 5mg                           | Paracet stikkpille 125mg       |
| Disprin spee disperg tab 300mg                          | Plavix tab 300mg               |
| Efedrin takeda inj 50mg/ml                              | Propolipid inf/inj 10mg/ml     |
| Esmeron inj 10mg/ml                                     | Propolipid inf/inj 10mg/ml     |
| Fentanyl hameln inj 50mcg/ml                            | Seloken inj 1mg/ml             |
| Flumazenil hameln inj 0,1mg/ml                          | Solu-Cortef inj subst 250mg    |
| Glukose braun inj 500mg/ml                              | Ster vann braun t par br Eco+  |
| Heparin leo inj 5000IE/ml                               | Trandate orifarm inj 5mg/ml    |

|                                                                                                                                                 |                               |
|-------------------------------------------------------------------------------------------------------------------------------------------------|-------------------------------|
| Isoprenalin NAF inj 0,2mg/ml                                                                                                                    | Tranexamic acid sir inj 100mg |
| Ketalar inj 50mg/ml                                                                                                                             | Ventoline inh væske 1mg/ml    |
| Other medications may be added or changed at short notice without warranting changes to this protocol or notifications to competent authorities |                               |

- Medications administered after end of Intervention will not be recorded in the CRF. Critically ill patients with long stays in the ICU such recording is beyond this trial.

## 5.6 Drug Accountability

The responsible site personnel will confirm receipt of IMP and will use the IMP only within the framework of this clinical study and in accordance with this protocol. Receipt, distribution and return will be documented in the TMF.

Specific systems based on the NorCRIN template for Drug accountability form and Investigational medicinal product-drug reconciliation form will be produced.

## 5.7 Drug Labelling

Both IMPs in this trial has a Marketing Authorization in the EU and is sourced from the EU market. They are used in the trial without modification and the packaging and labelling is carried out for local use only as per article 9.2. of the Directive 2005/28/EC (GCP Directive). We therefore apply for exemption from the specific labelling requirements for clinical trials.

## 5.8 Subject Numbering

Each subject is identified in the study by a unique subject number that is assigned when randomized. The subject number will match the number on the paper CRF that is found when opening the backpack holding the INOmax and the INOblender.

The number will be three digits, the first digit representing which site within the Oslo University Hospital study center.

1 denotes helicopter base Lørenskog

2 denotes physician manned ambulance 119

3 SAR helicopter based at Rygge

4 denotes Ullevål hospital Intensive care unit

5 denotes Rikshospitalet Intensive care unit

Other numbers may be added later

## 6 STUDY PROCEDURES

### 6.1.1 Before Treatment Starts

Recruiting doctor will receive a request from dispatch or the emergency department (ED). Information on SARS-COV-2 status and risk of exposure will be provided by the dispatch or the ED. This information combined with additional information obtained by the doctor prior to patient contact, determines whether the patient qualifies as confirmed, suspected or no COVID-19. Depending on all the gathered information, the doctor will decide whether to prepare the INO study kit. On first contact ( $t_{-1}$ ) the patient is screened for other inclusion/exclusion criteria, according to check-list on the CRF.

If eligible, the oxygen delivery system (such as open face mask, CPAP etc.) currently used is removed, and INO treatment kit is applied with Oxygen 10l/min on sealed face mask, PEEP set to 10 cm H2O, and INOBlender set to zero. Bag mask and PEEP valve with 100% O2 is considered better or equal to other non-invasive measures, available to patients in the ambulance service. O2 + 10 cmH2O PEEP is continued for 3 minutes. If SpO2 is <90% at this point, patient will be randomized to either INO or only O2 ( $t_0$ ). If SpO2 > 90% patients will be treated as per local guidelines outside study protocol.

### 6.1.2 Treatment

The doctor's assistant, who is specifically trained for the procedure, will open a sealed envelope with information on patient allocation, and either open or leave the INO cylinder closed accordingly. If randomized to only O2 a simulated cylinder opening will be undertaken. Regardless of randomization the INOBlender is set to deliver 20 ppm. SpO2 is recorded at time of allocation ( $t_0$ ) and after 5 minutes ( $t_1$ ). Other vital signs are automatically and continuously recorded in the internal memory of the patient monitor and extracted at 5 minute intervals to EOI ( $t_0$  to  $t_n$ ).

If the patient is included outside hospital, the doctor makes the decision to either perform RSI prior to transportation or continue current treatment during transport to hospital.

At the time the clinician decides to perform RSI, the lowest SpO2 during the RSI-procedure is recorded ( $t_{RSI}$ ) regardless of where the procedure is performed.

In any event where the bag/mask/valve is left idle, four normal tidal volumes must be ventilated into free air before re-connected to patient in order to purge the system of any NO2 build up.

Blood samples, physiological data and clinical scoring made after EOI is done as indicated by local routines regardless of the study. Relevant clinical data is retrieved from the institution's patient journal on follow-up at day 28 post admission.

### 6.1.3 End of Intervention

End of intervention is defined as the time point where INO administered by the INOBlender is discontinued.

This may be on different time points before transport, during transport or in hospital. For patients still requiring INO, the receiving hospital INO must be delivered by another INO device, and is no longer defined as IMP.

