|   |                                                                                                                                                                                        |                          | 1.2.1     | $\Delta \text{SpO}_2 (t_0\text{-}t_2)$                        | $\Delta \text{SpO}_2$ : change in $\text{O}_2$ saturation from $t_0$ to $t_2$ |  |
|   |                                                                                                                                                                                        |                          | 1.2.2     | $\text{SpO}_2$ during RSI ( $t_{\text{RSI}}$ )                | Lowest measured value                                                         |  |
|   |                                                                                                                                                                                        |                          | 1.2.3     | $\text{SpO}_2$ from $t_1 - t_n$                               | At 5 minutes intervals                                                        |  |
|   |                                                                                                                                                                                        |                          | 1.2.4     | Number of patients with $\text{SpO}_2 < 50$ from $t_1$ to EOI | EOI: end of intervention                                                      |  |
|   |                                                                                                                                                                                        |                          | 1.2.5     | Respiratory rate from $t_0$ to $t_{\text{RSI}}$ or EOI        | Calculated from impedance (ohms).                                             |  |
|   |                                                                                                                                                                                        |                          | 1.2.6     | $\text{PaO}_2$ at $t_0$ to EOI                                | Where available                                                               |  |

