## 8.2 Expected Adverse Events

### 8.2.1 Expected Adverse Events from Inhaled NO

Please consult the Summary of product characteristics for INOmax 800 ppm mol/mol medicinal gas for complete safety information.

In summary the most frequent expected AE is the rebound reaction, defined as “Abrupt discontinuation of the administration of inhaled nitric oxide may cause rebound reaction; decrease in oxygenation and increase in central pressure and subsequent decrease in systemic blood pressure. Rebound reaction is the most commonly adverse reaction in association with the clinical use of INOmax. The rebound may be seen early as well as late during therapy.”

The duration of therapy of INOmax in this SPC is up to 7 days in the peri-operative setting, and common treatment times are 24 -48 hours. In the present trial the treatment time is expected to be substantially shorter, we expect this to reduce the risk of all adverse events.

| Summary Of Product Characteristics 4.8 Undesirable effects |                  |             |                   |      |           |                                                           |
|------------------------------------------------------------|------------------|-------------|-------------------|------|-----------|-----------------------------------------------------------|
| System organ class                                         | Very common      | Common      | Uncommon          | Rare | Very rare | Not known                                                 |
| Blood and lymphatic system disorders                       | Thrombocytopenia | -           | Methemoglobinemia | -    | -         | -                                                         |
| Cardiac disorders                                          | -                | -           | -                 | -    | -         | Bradycardia (following abrupt discontinuation of therapy) |
| Vascular disorders                                         | -                | Hypotension | -                 | -    | -         | -                                                         |
| Respiratory, thoracic and mediastinal disorders            | -                | Atelectasis | -                 | -    | -         | Hypoxia
Dyspnoea
Chest Discomfort
Dry throat     |
| Nervous system disorders                                   | -                | -           | -                 | -    | -         | Headache
Dizziness                                     |

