### 8.3 Time Period for Reporting AE and SAE

- For each patient the standard time period for collecting and recording AE will be from allocation and until End of Intervention
- For each patient the standard time period for collecting and recording SAE will be from allocation and until the 28 day follow up visit. At the 28 days visit an assessment will be made where we specifically ask for all SAEs mentioned in chapter 8.2. We will also assess discharge notes and treating physician for other events that fulfil the SAE definition and that can be assessed by the study team.
- For patients still admitted to hospitals at day 28 an effort will be made to secure access to main discharge note for assessment for any SAE that has occurred between day 28 and discharge.
- Any information that comes to investigators attention for any included patient prior to End of Trial will be assessed according to this protocol

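### End of intervention is defined by the stop of INO, so the windows for the SpO2 <50 and cardiac-arrest counts and for non-serious AE recording depend on treatment response, and the control-arm stop is not named

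*Protocol*

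**What the plan says.** **Definition.** Section 6.1.3 reads: "End of intervention is defined as the time point where INO administered by the INOBlender is discontinued". It adds: "This may be on different time points before transport, during transport or in hospital". No separate wording covers patients given oxygen only.

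**Control arm.** Section 6.1.2 says: "Regardless of randomization the INOBlender is set to deliver 20 ppm". In controls the cylinder stays closed and "a simulated cylinder opening will be undertaken".

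**When INO stops.** Under section 5.3, "a dose reduction of iNO should be attempted if SpO 2 ≥ 94% after 5 minutes". Steps are 5 ppm every 5 minutes and are halted if SpO2 falls more than 5 points below its t1 value. Other patients are weaned after hospital arrival, once intubated or once a decision not to intubate is made. INO may be prolonged if rebound is suspected. Section 3 estimates one hour for the intervention and warns of wide variation.

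**What the end of intervention (EOI) closes.**
- Endpoint 1.2.4 in section 2: "Number of patients with $\text{SpO}_2 < 50$ from $t_1$ to EOI".
- Endpoint 1.2.7, cardiac arrest during intervention.
- The 5-minute extraction of vital signs (6.1.2).
- AE recording (8.3): "the standard time period for collecting and recording AE will be from allocation and until End of Intervention".

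SAEs are collected to day 28.

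**Rebound.** Section 8.2.1 cites the product information: "Abrupt discontinuation of the administration of inhaled nitric oxide may cause rebound reaction". Its table also lists bradycardia after abrupt discontinuation.

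**The concern.** A count of events up to EOI compares the arms fairly only if both are watched for the same time, or if the time watched does not depend on treatment. Here a patient who improves by t1 starts the step-down and leaves the window early, and a patient who does not stays in it until hospital. If INO works on the primary endpoint, the INO arm has less time in which an event can be counted. It could then show fewer events of 1.2.4 and 1.2.7 without any effect on the hazard.

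A related gap concerns intubation. Section 5.3 allows weaning whether or not RSI has been done, and 6.1.2 allows RSI to wait until hospital. A responder may thus be weaned first and intubated after EOI. A fall below 50% or an arrest during that RSI would not count, while the same event in a patient still on INO would.

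Endpoint 1.2.4 also starts at t1. Exclusion criterion 1 ensures that every patient is at 50% or above at t0, and 6.2 allows unblinding for values below 50% from allocation onward. A fall in the first 5 minutes, the one interval of equal length in both arms, could lead to unblinding and still go uncounted.

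On safety, heart rate, blood pressure and non-serious AEs stop being recorded at the moment after which rebound and bradycardia are described as occurring.

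**Working it through.** **1. The plan's own figure.** The only reproducible figure nearby is the sample size. SD of change = sqrt(2 × 10² × (1 − 0.8)) = 6.32. For a 5-point difference at two-sided 5%, a t-test has power 0.798 with 26 per arm and 0.813 with 27. So 27 per arm (54) is confirmed. It rests on SpO2 at 5 minutes and does not involve EOI.

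**2. Earliest EOI under 5.3.** 15 ppm at 5 min, 10 at 10 min, 5 at 15 min, 0 at 20 min. A patient at 94% or more at t1 can leave at about 20 min. For the others, take L = 60 min (the section 3 estimate), or L = 80 min if a 20-minute in-hospital wean is added.

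**3. Mean window by arm.** If a share p reaches 94% at t1, the mean window is 20p + L(1 − p). The protocol gives no shares, so four control/INO pairs are assumed.

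| Control / INO share | L = 60: control, INO (min) | L = 80: control, INO (min) |
|---|---|---|
| 20% / 40% | 52, 44 | 68, 56 |
| 20% / 50% | 52, 40 | 68, 50 |
| 30% / 60% | 48, 36 | 62, 44 |
| 10% / 70% | 56, 32 | 74, 38 |

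**4. Expected events with the same constant hazard in both arms.** With an event probability q per 60 min (assumed 10% to 30%), the hazard is h = −ln(1 − q)/60. The expected proportion in an arm is p(1 − e^(−20h)) + (1 − p)(1 − e^(−Lh)).

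Example with q = 20%, shares 20% and 50%, L = 60: 1 − 0.8^(1/3) = 0.0717.
- Control: 0.2 × 0.0717 + 0.8 × 0.20 = 0.174, or 4.7 of 27.
- INO: 0.5 × 0.0717 + 0.5 × 0.20 = 0.136, or 3.7 of 27.
- Ratio: 0.78.

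Over the four pairs and all q, the INO/control ratio is 0.58 to 0.86 for L = 60 and 0.52 to 0.84 for L = 80. With equal shares it is 1.00. A narrower gap moves it toward 1: shares of 30% and 40% with q = 20%, L = 60 give (0.4 × 0.0717 + 0.6 × 0.20)/(0.3 × 0.0717 + 0.7 × 0.20) = 0.149/0.162 = 0.92.

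**5. Start at t1.** For 1.2.4 the windows are 5 minutes shorter, 15 and 55 min. In the example pair the mean windows become 0.2 × 15 + 0.8 × 55 = 47 min and 0.5 × 15 + 0.5 × 55 = 35 min, a ratio of 0.74 against 40/52 = 0.77 from t0. The later start makes the imbalance slightly larger.

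**6. If responders have a lower hazard.** Take the example with half the hazard in responders: 1 − 0.8^(1/6) = 0.0365 over 20 min and 1 − 0.8^(1/2) = 0.1056 over 60 min.
- To-EOI window: (0.5 × 0.0365 + 0.10)/(0.2 × 0.0365 + 0.16) = 0.118/0.167 = 0.71.
- Full 60 min: (0.5 × 0.1056 + 0.10)/(0.2 × 0.1056 + 0.16) = 0.153/0.181 = 0.84.

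Part of the difference is then a real effect and part comes from the window. If responders had no events at all, the two windows would agree.

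**7. AE collection after EOI.** Section 8.3 ends AE recording at EOI and continues SAEs to day 28. Section 6.1.4 describes collecting adverse events at follow-up for the period from EOI to day 28. The two disagree on non-serious events.

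**The case against.** Several stronger readings are tempting, and the protocol does not support them.

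**That EOI has no meaning in controls.** The blender setting and the simulated opening give controls an operational stop, and the study doctor is blinded. Section 10.3 already defines the analysis sets by the blender setting, without reference to arm. What remains is a gap in the wording of 6.1.3.

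**That rebound goes unobserved.** Section 8.2.2 requires suspected rebound to be reported as an SAE, and SAEs run to day 28 in both arms. At that visit the events listed in 8.2, including bradycardia and hypotension, are asked for. Stepwise weaning under observation also means that some rebound would appear before EOI. This protection is partial, however. It depends on someone suspecting rebound, and it supplies neither a vital-sign series after the stop nor a rate of non-serious events. The sentence in 8.2.2 also leaves unclear whether its limit to the time before EOI applies to rebound as well as to death.

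**That the arms could differ 3.5-fold.** At an assumed 1% per 5 min, a 15-minute window gives 1 − 0.99³ = 2.97% and a 55-minute window 1 − 0.99¹¹ = 10.47%, a ratio of 3.52. This sets one responder against one non-responder. It would be a between-arm ratio only if every INO patient and no control responded.

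**That every endpoint read to EOI is distorted.** Time-indexed series lose later observations, but values at common time points stay comparable. Endpoint 2.3.1 allows the first sample after EOI, and 1.2.2 is recorded wherever RSI takes place.

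The objection that equal hazards are implausible also has force: patients at 94% are less likely to fall below 50%, so truncation loses fewer events than the equal-hazard figures suggest.

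**Conclusion.** The point holds for endpoints 1.2.4 and 1.2.7, for non-serious AEs, and for heart rate and blood pressure after the stop. Followed as written, the plan gives the arms unequal time at risk whenever response at t1 differs between them. Under equal hazards and the assumed shares, the expected event ratio is about 0.5 to 0.86 where it should be 1.

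The size rests on response shares, hazards and an L of 60 to 80 minutes, of which the protocol gives only the one-hour estimate. A smaller difference in response or a lower hazard in responders shrinks the distortion. Prolonging INO for rebound lengthens the INO window and could reverse its direction.

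The primary endpoint, 1.2.1, 1.2.2, 2.3.1, the day-28 outcomes and N = 54 are not affected. Severity: should be fixed. It concerns two secondary counts and part of the safety record in a phase II trial. It belongs in the protocol because EOI decides what is collected, and non-serious events not recorded at the time cannot be reliably recovered.

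**What to change.** 1. In 6.1.3, define EOI in both arms as the time when the INOBlender is set to zero, real or sham.
2. In section 2, count 1.2.4 and 1.2.7 over one fixed clock window from t0 in both arms (for example t0 to 60 min), regardless of when INO stops. This also brings in the interval from t0 to t1.
3. Reconcile 6.1.4 with 8.3, and extend the extraction in 6.1.2, so that AEs, heart rate and blood pressure are recorded for the same fixed period after the stop in both arms. State in 8.2.2 whether mandatory reporting of suspected rebound continues after EOI.

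The weaning rules in 5.3 and the sample size need no change for this.

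The cost is wording in five sections and a somewhat longer extraction of monitor and chart data. The drawback is that a fixed window will include some time on INO that is no longer the IMP, and some time after the receiving team has learned the allocation. Drugs given after EOI are not recorded in the CRF. The to-EOI version of 1.2.4 and 1.2.7 can therefore be kept as a supportive analysis.
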